#### Secondary Outcomes

##### NIH Examiner

The NIH EXAMINER battery is important to address transfer effects to untrained domains, such as executive function, insight or social cognition and behavior. Chi-square tests will be used for week 3 and 6 reliable change indexes. Reliable Change Index (RCI) will be calculated by using the standard deviation of the reference data-set, and the test-retest reliability (Cronbach’s alpha). As we want the RCI, the difference between measurements will be compared to the S_Diff_ multiplied by 1.96 (Jacobson and Truax, 1991). This will allow for a categorial YES/NO variable for the chi-square tests. Moreover, with the present design, we can track the intervention effects in several time points, namely at baseline, week 3 and 6 of the treatment. This will be performed by means of chi-squares, with time as within subject factor and intervention as between subject factor.

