### Sample Size

No previous studies using tACS and SoP have used UFOV as a primary outcome, and as such, we are using the UFOV test-retest data from Bentley et al. (2012). For older adults the mean (SD) test-retest difference (i.e., consistency between measurements at two different timepoints on the same sample) between UFOV applications was 56.2 (74.8). In order to show an effect, our intervention should at least surpass the mean test-retest difference. So we ran three different scenarios: 0.50, 0.75, and 1.00 SD below mean difference for older adults, with a power of 0.8 and alpha of 0.05. In these scenarios, a minimum of 17 participants and a maximum of 64 per group would be required in order to detect a Cohen’s d of 1 and 0.5, respectively. However, these values were above the mean test-retest difference for younger adults, namely 31.5 (43.7). As such we used this value as our cut off point, and with a power of 0.8 and alpha of 0.05 we would need at least 98 participants per group. If an attrition rate of 10% is considered, 109 participants per group will be required. However, having trial feasibility into consideration, we decided to conduct a interim analysis for futility as soon as 19 participants per group are reached, then at 32 participants per group and finally at 71 participants per group (always considering the 10% attrition rate).

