##### Long-Term Effects

Assessments at 3 and 6 months of follow-up will be critical for understanding the longterm effects of the intervention. We will use the reliable change index (RCI; Ferguson et al., 2002) for the primary (i.e., UFOV) and secondary endpoints such as the NIH EXAMINER. By assessing if the changes in test scores are reliable across those time points, our understanding about the long lasting effects of the intervention will improve, while potential placebo effects that are not expected to persist for that long will be mitigated. This will be performed by means of Chi-squares, with time as within subject factor and intervention as between subject factor. At the 1, 3, and 6 month follow-ups, participants will also perform the EEG, in order to allow for the correlation between changes in α- power, Event Related Desynchronization (ERD; for alpha attenuation), Phase amplitude coupling (PAC; mainly α−γ) and with the reliable change indexes (RCI) from the primary (UFOV) and secondary outcomes (NIH EXAMINER), which will increase our understanding about the mechanisms underlying this intervention.

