Another important aspect of this study protocol is the understanding of the long-term effects of the intervention. The first follow-up assessment will occur at 1 month after the intervention has ended, and will be repeated at 3 and 6 months (see Figure 2). These long-term assessments are extremely important, as there is substantial evidence for placebo effects in healthy volunteers due to CT. In a recent study, participants that responded to a catchy flyer, suggesting that they were going to undertake a 1 h CT that would improve their cognitive performance and their fluid intelligence, improved between 5 and 10 points in a standard IQ scale; while those that responded to a nonsuggestive flyer (i.e., participating in a 1 h session in exchange for course credits) did not (Foroughi et al., 2016). This study highlights the importance of accounting for placebo effects when assessing the effects of CT. Despite the fact that there is no clear framework for estimating the duration of placebo effects, there are suggestions that the placebo effects may last up to 6 or 12 months (Hansen et al., 1996; Previtali et al., 2021). We will be using reliable change index (RCI) in order to assess if the changes in participant’s performance across time are reliable or not (Barker-Collo and Purdy, 2013). By using multiple assessments and especially the RCI we expect to mitigate any possible confounders arising from placebo effects.

The main challenge will be the loss to follow-up. Nonetheless, the team will focus on developing strategies to minimize this, such as sending reminders (phone, letter or email), by involving caregivers in the process, among others. If participants are not able (or willing to perform the EEG during follow-up), they will be offered the opportunity to perform the remaining follow-up assessments remotely, using videoconference systems, by phone or by the means of server based cognitive tasks.

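### The NIH EXAMINER reliable-change rule uses Cronbach's alpha as its test-retest coefficient, and an undirected YES/NO cut is the only stated arm comparison for transfer and durability

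*Protocol article*

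**What the plan says.** Under Statistical Analysis, NIH Examiner, the protocol article computes the RCI from "the standard deviation of the reference data-set" and "the test-retest reliability (Cronbach’s alpha"). It then states that "the difference between measurements will be compared to the S_Diff_ multiplied by 1.96", and adds: "This will allow for a categorial YES/NO variable for the chi-square tests". The tests are chi-squares at weeks 3 and 6, and again across baseline, week 3 and week 6.

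Under Long-Term Effects, the RCI with chi-squares is used again, "for the primary (i.e., UFOV) and secondary endpoints such as the NIH EXAMINER". The same paragraph says that "potential placebo effects that are not expected to persist for that long will be mitigated". The Discussion says that "the placebo effects may last up to 6 or 12 months" and still expects the RCI to help against placebo confounding.

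The EXAMINER is described under Outcomes and under Assessments as yielding a composite score. Only UFOV at weeks 3 and 6 is compared between arms as a continuous change (Statistical Analysis, Primary Outcome).

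**The concern.** Three things on the page need attention.

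- **The coefficient.** S_Diff is meant to be the standard deviation of the difference between two sittings of an unchanged person. That requires stability between sittings. Cronbach's alpha measures how well items agree within one sitting. Equating them sets the cut at an unknown multiple of the true retest SD.
- **The dichotomy.** YES means only that the difference is set against 1.96 × S_Diff. No direction is given, so a reliable decline could count as YES. A chi-square on this variable is the only stated test of transfer and of durability between arms, and both are stated aims of the trial.
- **The placebo rationale.** Long-Term Effects relies on placebo effects fading by 3 to 6 months, and the Discussion reports suggestions that they can last that long or longer. The RCI asks whether a change exceeds measurement error. It says nothing about the cause of the change.

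At stake are how far the label 'reliable' can be trusted and the chance of detecting transfer or a lasting effect if there is one.

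**Working it through.** **1. Reproducing the plan's own sample size (Sample Size section, UFOV).** Test-retest difference 56.2 (SD 74.8) in older adults and 31.5 (SD 43.7) in younger adults; power 0.80; alpha level 0.05, taken as two-sided.

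- Difference: 56.2 − 31.5 = 24.7
- SD: √((74.8² + 43.7²)/2) = √3752.4 = 61.26
- d = 24.7/61.26 = 0.403
- Two-sample t-test: 98 per group, as stated (normal approximation: 97). With 10% attrition, 98/0.9 = 108.9, so 109; 3 × 109 = 327.

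The plan's figure is reproduced. It concerns UFOV; no power is stated for the RCI analyses.

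**2. What the choice of coefficient does to the cut.** S_Diff = SD × √(2(1 − reliability)). If alpha is entered but the true retest reliability is r, the effective cut in true SDs of change is 1.96 × √((1 − alpha)/(1 − r)). The false-change rate is 2 × (1 − Φ(cut)). The document gives neither alpha nor r, so all values below are assumed.

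| alpha | r | effective cut | unchanged people labelled as changed |
|---|---|---|---|
| 0.90 | 0.70 | 1.13 | 25.8% |
| 0.90 | 0.80 | 1.39 | 16.6% |
| 0.85 | 0.80 | 1.70 | 9.0% |
| equal | equal | 1.96 | 5.0% |
| 0.80 | 0.90 | 2.77 | 0.6% |

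The error can go either way: too many YES if alpha exceeds r, too few if it is below r.

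**3. What the dichotomy costs.** Assume normal change scores with SD 1, 98 per group, two arms differing by d = 0.403, and the cut at 1.96 SD (the nominal rule). The comparison arm shifts by m. One scenario for m comes from the UFOV figures: 56.2/74.8 = 0.75 SD.

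At m = 0.75, counting improvement only:

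- p0 = P(Z > 1.96 − 0.751) = 0.113
- p1 = P(Z > 1.96 − 0.751 − 0.403) = 0.210
- Pooled-variance comparison of two proportions: power 45%; 226 per arm needed for 80%

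Counting YES in either direction: p0 = 0.117, p1 = 0.211; power 43%; 241 per arm.

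Against 97 per arm for the continuous score, 226/97 = 2.3 and 241/97 = 2.5, so 97/241 to 97/226 = 40–43% of the information is kept. A simulation of 20,000 trials gave 44% (either direction) and 47% (improvement only), against 80% for the continuous score.

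| shift m (SD of change) | power, either direction / improvement only | information kept |
|---|---|---|
| 0 | 8% / 23% | 4% / 18% |
| 0.5 | 33% / 38% | 29% / 34% |
| 0.75 | 43% / 45% | 40% / 43% |
| 1.0 | 51% / 52% | 50% / 51% |
| 1.96 (cut at the median) | 60% / 60% | 63% / 63% |

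**4. The two effects interact.** If alpha exceeds r, the real cut is lower and less is lost. At alpha 0.90, r 0.80 and m = 0.75, the cut is 1.39 and 50–59% of the information is kept.

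**The case against.** Much can be said for the plan.

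- **The label may be a slip.** The phrase names both coefficients, so a proper retest value may be intended. That is possible, but the text as it stands identifies the two, and an analyst following it would be entitled to use alpha.
- **The arm comparison is not biased.** A wrong S_Diff, or a retest gain that is not subtracted, applies alike to all randomised arms. This stands: the chi-square null remains valid and only the individual label is affected.
- **Detail may sit elsewhere.** A fuller protocol or analysis plan could fix the direction of YES or add an analysis of the composite. That limits how much weight the missing direction carries. It does not change the fact that the article names a test, and names the weaker one.
- **The stakes are limited.** The trial calls itself exploratory, these outcomes are secondary, and UFOV at weeks 3 and 6 is analysed as continuous. All true.

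A reader might also infer more than the document supports:

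- *That ordinary retest variation will be over-called as reliable change.* This needs alpha above r, which is not stated.
- *That the dichotomy keeps only 14% of the information and needs up to seven times the participants.* That is a calculation for small effects with no average improvement in the comparison arm, whereas the plan expects all groups to improve.
- *That 11.3% of untreated people would pass the cut.* This carries UFOV figures into a rule stated for the EXAMINER and reads 56.2 as a signed gain. The Sample Size section describes it as consistency between two measurements. Here 0.75 SD serves only as a scenario.
- *That the alpha error also affects UFOV at follow-up.* Long-Term Effects does not restate the coefficient.
- *That a 6-month result would be presented as free of placebo effects.* The text says mitigated.

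**Conclusion.** The point holds in a bounded form. The coefficient named for the EXAMINER index is the wrong kind, so the 5% meaning of the 1.96 cut is not secured; the size and direction of the error are unknown. The undirected dichotomy is the only stated arm comparison for the EXAMINER at any visit and for UFOV after week 6. In a scenario built from the plan's own figures it roughly halves power, from 80% to about 43–45%, which is equivalent to needing 2.3–2.5 times the participants. This rests on carrying UFOV's d of about 0.40 and the 0.75 SD shift over to the EXAMINER, on normal change scores, and on a cut at 1.96 true SDs. The loss is greater with a smaller common shift and less when the cut lies nearer the median.

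The two statements on the duration of placebo effects do conflict, and the RCI cannot resolve that. The change is worth making for the secondary outcomes; the primary UFOV conclusions do not depend on it.

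**What to change.** 1. Make the stated arm comparison of the EXAMINER composite (weeks 3 and 6 and the follow-up visits), and of UFOV at follow-up, a continuous analysis adjusted for the baseline score.
2. Keep the RCI as a supportive display. Name a true test-retest coefficient over a comparable interval and its source, and count reliable improvement separately from reliable decline.
3. Reconcile Long-Term Effects with the Discussion on how long placebo effects may last. Remove the claim that the RCI mitigates them, and let durability rest on the contrast between arms at each follow-up.

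Cost: analysis wording only. No new data, visits or participants are needed.

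### The only reliable-change rule given subtracts no expected retest change; if it also governs UFOV at follow-up and S_Diff is near 74.8, retest alone would label about 11.7% rather than 5% as reliably changed

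*Protocol article*

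**What the plan says.** All references are to the protocol article.

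- **Statistical Analysis, NIH Examiner.** The RCI is calculated "by using the standard deviation of the reference data-set, and the test-retest reliability", with Cronbach's alpha named in brackets as the reliability. Then "the difference between measurements will be compared to the S_Diff_ multiplied by 1.96". The result is a YES/NO variable for chi-square tests at weeks 3 and 6. No mean retest change enters the rule, and no value is given for the reference SD, the reliability or S_Diff.
- **Sample Size.** The mean (SD) UFOV retest difference is 56.2 (74.8) in older adults and 31.5 (43.7) in younger adults. The section adds: "In order to show an effect, our intervention should at least surpass the mean test-retest difference".
- **Long-Term Effects.** An RCI is to be used for both UFOV and the NIH EXAMINER at follow-up. The section cites a different RCI source from the NIH Examiner section and states no formula. It treats reliable change at follow-up as evidence of lasting effect and as a way to mitigate placebo effects. The Discussion repeats the placebo argument and singles out the RCI.
- **Primary Outcome (analysis).** UFOV at weeks 3 and 6 is analysed by ANOVA on change from baseline, not by the RCI. All groups are expected to improve.
- **Discussion.** The design has no placebo-only arm.

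**The concern.** A rule that compares the raw difference with 1.96 x S_Diff asks whether a person's change is larger than measurement error around zero change. When the trial is sized, the plan asks something else: whether change exceeds what a second test produces without any intervention. If scores shift on retest, the zero-centred rule labels some people as reliably changed only because they have met the test before.

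This matters because the label carries interpretive weight. Assessments are similar at every study point, so in the analyses with time as a within-subject factor, time runs together with repeated testing. A YES at follow-up is to be read as a durable effect, and the RCI is relied on to deal with placebo effects. A zero-centred index cannot separate either from practice.

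There is also a problem of direction. Read literally, a bare difference that yields YES/NO counts a reliable decline as YES.

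**Working it through.** **1. The plan's own figures.** The document states no false-label rate, but its sample size uses the same retest numbers and reproduces.
- Difference: 56.2 - 31.5 = 24.7.
- Pooled SD: sqrt((74.8² + 43.7²)/2) = 61.26, so d = 24.7/61.26 = 0.403.
- A two-sided t-test at alpha 0.05 and power 0.8 needs 97.5, so 98 per group. Then 98/0.9 = 108.9, so 109 per group, and 3 x 109 = 327 in total.

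The retest means are thus used as shifts on a common scale. That fits reading 56.2 as a signed gain, although the text does not say so.

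**2. The rule applied to retest alone.** Assumptions: the NIH Examiner rule is also used for UFOV; change without intervention is D ~ Normal(56.2, 74.8); S_Diff = 74.8.
- Cut-off: 1.96 x 74.8 = 146.6.
- Improvement: P(D > 146.6) = P(Z > (146.6 - 56.2)/74.8) = P(Z > 1.209) = 11.3%, against 2.5% nominal.
- Opposite direction: P(D < -146.6) = P(Z < -2.711) = 0.3%.
- Total: 11.7%, against 5% nominal, or 2.3 times. Subtracting 56.2 first returns 5.0%.
- Per arm of 98, improvers from retest alone: 98 x 0.113 = about 11, against 98 x 0.025 = about 2.5.
- Younger-adult figures (31.5, SD 43.7, S_Diff = 43.7): 10.8% in the improvement direction, 11.1% in total.

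**3. Dependence on S_Diff.** D stays Normal(56.2, 74.8). The last column applies the same cut-off after subtracting 56.2.

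| S_Diff | Improvement | Total, rule as written | Total, retest mean subtracted |
|---|---|---|---|
| 60 | 20.6% | 21.6% | 11.6% |
| 70 | 13.9% | 14.4% | 6.7% |
| 74.8 | 11.3% | 11.7% | 5.0% |
| 80 | 8.9% | 9.2% | 3.6% |
| 90 | 5.4% | 5.5% | 1.8% |
| 100 | 3.1% | 3.1% | 0.9% |

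The total is above 10% only for S_Diff below about 78, and it reaches 5% at about 92. In the improvement direction the rate stays above 5% (twice nominal) up to about 91. In every row the uncentred rule labels more people than the centred one.

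**4. Shape of the distribution, S_Diff = 74.8.** Skewness of 0.5 to 2 gives 11.0% to 11.8% in total. Heavy-tailed t distributions give 11.0% (10 df), 10.3% (6 df) and 9.1% (4 df).

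**5. NIH EXAMINER.** The document gives no retest shift. Purely as an illustration, assume practice of 0.25, 0.5 or 0.75 S_Diff and an SD of change equal to S_Diff. The improvement rate P(Z > 1.96 - k) is then 4.4%, 7.2% or 11.3%.

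**6. Between-arm test.** With the same 11.7% YES rate in three arms of 98, the simulated size of the chi-square at nominal 5% is 0.050.

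**The case against.** Most of the case on the other side stands, and it limits the point.

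- **Rule and figure belong to different instruments.** The formula is under NIH Examiner and 56.2 is a UFOV figure. The bridge is Long-Term Effects, which cites another source without a formula. The UFOV index might already be practice-adjusted, and the document does not settle it.
- **S_Diff is not given.** It is to come from a reference SD and a reliability, not from the 74.8 used above. A reader might infer that practice is bound to be mislabelled at more than twice the nominal rate. That fails once S_Diff exceeds about 78, or with very heavy tails. A smaller S_Diff makes matters worse.
- **The sign of 56.2 is not stated.** The text glosses the figure as consistency between measurements. A signed gain fits its use in Sample Size but remains an inference.
- **Scope.** A reader might infer that UFOV is classified this way at every post-baseline visit. The document specifies the RCI for UFOV only at follow-up: 3 and 6 months, with 1 month added in the EEG correlations.
- **Randomised comparison.** A reader might infer that nothing separates training from practice, or that the chi-square is invalid. Neither is supported. The abstract names active α-tACS alone as a comparator, and the SoP section describes a sham task with fixed exposure. That arm takes the same tests, so its contrast with combined treatment controls for test practice. Equal practice does not inflate the test (step 6).
- **The remedy borrows a mean.** The older-adult figure is not said to come from people with MCI, and no retest interval is given.

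The objection does not remove the gap itself. The one formula that the document fixes omits the retest change that the same document says an effect should exceed, and the RCI is still relied on for durability and placebo.

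**Conclusion.** The point holds in a conditional form. The only RCI formula in the document is centred on zero change and, as written, counts decline as YES. The 11.7% against 5% (11.3% against 2.5% for improvement) needs three assumptions that the document does not confirm: the same rule governs UFOV at follow-up, 56.2 is a signed gain, and S_Diff is near 74.8. Across S_Diff from 60 to 100 the total runs from 21.6% to 3.1%. The EXAMINER rate cannot be determined.

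The damage is confined to individual labels, to within-arm and over-time YES proportions, and to the argument that the RCI shows lasting effects and mitigates placebo. The randomised comparison of YES proportions keeps its type I error under equal practice, and the primary ANOVA does not use the RCI. The rule should be corrected, but the flaw does not undermine the trial's main test.

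**What to change.** - State one RCI rule for both instruments, with the numerical inputs to S_Diff (reference SD and reliability coefficient) and their sources.
- Subtract the expected retest change before comparing with 1.96 x S_Diff. For UFOV use the older-adult mean already quoted in Sample Size, noting that it is not stated to come from people with MCI. For the EXAMINER use the retest mean of the reference data set where one is available.
- Define YES as reliable improvement only, say which direction of change is improvement for each instrument, and report reliable decline as a separate category.
- State in Long-Term Effects and the Discussion that within-arm YES proportions are not read as treatment benefit; that reading rests on the comparison between arms.

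The cost is a revised definition and the work of sourcing its inputs, with no change to design, sample size or data collection. Fewer participants will be classed as reliably improved, so the reported proportions will look less favourable.

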### Statistical Analysis

#### Primary Outcome

We expect that all groups, after the intervention, have increased performance in the UFOV scores, however we also expect that the group with the combined active α-tACS and SoP training would present the largest increase in scores, when comparing to either intervention alone. This will be tested by calculating the delta (week 3 or 6—baseline), and by performing independent one-way ANOVAS with intervention as a factor. Moreover, with the present design, we can track the intervention effects in several time points, namely between baseline, at week 3 and 6 of the interventions. This will be performed by means of an exploratory mixed model-ANOVAS, with time as within subject factor and intervention as between subject factor. As we cannot control at this point for several variables such as gender, depression or years of education, if there are significant differences between groups after randomization, we will include those covariates in the analysis, performing ANCOVAS instead of ANOVAS.

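### The NIH EXAMINER reliable-change analysis lists baseline as a time level, where the YES/NO variable can only be NO; this inflates the test of the time effect, but not the comparisons between arms

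*Protocol article*

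**What the plan says.** All of this is in the Statistical Analysis part of the protocol article.

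- **Variable (NIH Examiner).** Reliable change rests on a difference: "the difference between measurements will be compared to the S_Diff_ multiplied by 1.96". The result is binary: "This will allow for a categorial YES/NO variable for the chi-square tests".
- **First analysis (NIH Examiner).** "Chi-square tests will be used for week 3 and 6 reliable change indexes". Baseline is not a level here.
- **Second analysis (NIH Examiner).** The section then adds tracking over repeated visits: "namely at baseline, week 3 and 6 of the treatment. This will be performed by means of chi-squares, with time as within subject factor". The between-subject factor is intervention.
- **Parallel text (Primary Outcome).** The UFOV is followed over time points, "namely between baseline, at week 3 and 6 of the interventions", by "exploratory mixed model-ANOVAS, with time as within subject factor and intervention as between subject factor". The UFOV has a score at baseline, so a baseline level is valid there.

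**The concern.** A change indicator needs two measurements. The protocol defines none before baseline, so the only value available at baseline is NO (change of zero) or none at all. Listing baseline beside weeks 3 and 6 as a level of the time factor puts a structural zero into the table.

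The cut-off of 1.96 × S_Diff is built to flag a small share of people who have not changed. Setting that share at weeks 3 and 6 against a fixed zero produces a time effect without any intervention or practice effect.

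This is separate from the question of whether an ordinary chi-square suits repeated measurements on the same people. A test made for paired binary data meets the same forced zero. At stake is the reading of the EXAMINER results over time. The Discussion expects all groups to improve, and an artificial rise from baseline would appear to agree with that.

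**Working it through.** **1. Size of the test.** The protocol gives no figure for this analysis, so I take its evaluable sample size: "with a power of 0.8 and alpha of 0.05 we would need at least 98 participants per group", then "If an attrition rate of 10% is considered, 109 participants per group will be required". These figures can be reproduced.

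- The two test-retest differences in the Sample Size section are 56.2 (SD 74.8) and 31.5 (SD 43.7). Their difference is 24.7.
- The pooled SD is √((74.8² + 43.7²)/2) = 61.26, so d = 24.7/61.26 = 0.403.
- With two-sided alpha 0.05 and power 0.80, the t-based calculation gives 97.5, hence 98 per group.
- 98/0.90 = 108.9, hence 109, and 3 × 109 = 327 in total.
- Evaluable: 98 per arm, 3 × 98 = 294 pooled.

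Pooling the two SDs is my reconstruction; the protocol does not state it.

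**2. Chance flag rate (assumed).** With no true change, normal errors and a correct S_Diff, the cut-off flags p = 5% at each later visit if either direction counts as YES, and p = 2.5% if only improvement counts. The text does not say which direction counts, so both are carried through.

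**3. Expected table.** The YES shares are 0, p and p at baseline, week 3 and week 6, with mean 2p/3. The Pearson chi-square on 2 df simplifies to

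χ² = N × [(2p/3)² + 2(p/3)²] / [(2p/3)(1 − 2p/3)] = N × p / (1 − 2p/3), and the p-value is exp(−χ²/2).

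| N | p | χ² | p-value |
|---|---|---|---|
| 294 (pooled) | 5% | 14.7/0.9667 = 15.2 | 0.0005 |
| 294 (pooled) | 2.5% | 7.35/0.9833 = 7.5 | 0.024 |
| 98 (one arm) | 5% | 4.9/0.9667 = 5.1 | 0.08 |
| 98 (one arm) | 2.5% | 2.45/0.9833 = 2.5 | 0.29 |

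In the pooled case, the table expected when nothing has happened is already significant. In a single arm it is not.

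**4. Simulated rejection rates at nominal 5%, no true change.** The correlation between the two changes is assumed to be 0.3 to 0.7.

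| Time test (Pearson) | Either direction | Improvement only |
|---|---|---|
| Pooled, baseline included | about 100% | 83-87% |
| One arm, baseline included | 46-51% | 10-14% |

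With weeks 3 and 6 only, the pooled test rejects in 2-5%.

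A separate simulation, assuming retest reliability 0.80 (3,000 runs per setting), agrees. With baseline included, the pooled Pearson test rejects in 100% (either direction) and 86% (improvement only). Within one arm the rates are 49% and 13%. Cochran's Q does no better: 100% and 90% pooled, 60% and 20% within one arm. With weeks 3 and 6 only, Pearson gives about 3-4% and McNemar about 4-6%.

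**5. Comparisons between arms.** Under the same null, the comparison of the three arms at week 3 rejects in 4.4-5.0%. Baseline does not enter a comparison made within one visit, so the same reasoning holds at week 6. A test of whether the arm pattern differs across time rejects in 2-4%.

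**The case against.** **Baseline may only describe the schedule.** The section has already tied the reliable-change indexes to weeks 3 and 6, no sentence assigns an index at baseline, and the Long-Term Effects section uses similar chi-square wording without a baseline level. Changes between all pairs of visits would also use three time points. An analyst might therefore never create a baseline column. This reading is possible, but it is not what the sentence says. The week 3 and 6 test is stated separately, and the added analysis names baseline as one of the time points and makes time a within-subject factor. The text needs correcting even if the intention was sound.

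**A reader might infer a false treatment difference.** An omnibus table of all nine arm-by-time cells does reject in about 90-93% of null trials when either direction counts. That only restates the unequal time margin; it is not an interaction test. Step 5 shows that the comparisons between arms keep their level, so no spurious advantage for any arm follows.

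**A reader might infer that a repeated-measures logistic model could not be fitted at all.** That is too strong. Only the baseline contrast cannot be estimated; arm effects at weeks 3 and 6 still can.

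**The consequence is limited.** The trial's question is whether the combination beats either intervention alone. The Discussion states that there is no placebo-only arm, so a time effect pooled over arms could not establish transfer even if tested correctly. This stands, and it lowers the weight of the point.

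**Conclusion.** The sentence is wrong as written, within a narrow scope. Taken literally, it makes the pooled test of time on EXAMINER reliable change reject almost always when either direction counts, and in 83-87% of trials when only improvement counts. Within one arm the error is inflated (46-51% or 10-14%) but rejection is far from certain.

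The sizes rest on assumptions outside the document: 5% or 2.5% flagged by chance, normal errors, a correct S_Diff, and a correlation of 0.3 to 0.7 between the two changes. That baseline can hold no YES needs none of these; it follows from the protocol's own definition.

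The comparisons between arms at week 3 and week 6 and the primary UFOV analysis stand. This is an additional analysis of a secondary outcome in a trial that the protocol calls exploratory, so the severity is minor.

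**What to change.** In the NIH Examiner section, restrict the time factor of the reliable-change analysis to week 3 and week 6, and state that the baseline EXAMINER score serves only as the reference from which change is computed. If a course that includes baseline is wanted, analyse the EXAMINER score itself at baseline, week 3 and week 6, as the Primary Outcome section does for the UFOV.

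The cost is one sentence. No new data and no further participants are needed. The change is best made before any results are seen.

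### An ordinary chi-square cannot take time as a within-subject factor, so the planned across-visit tests of reliable change are not valid as written

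*Protocol article*

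**What the plan says.** Under Statistical Analysis, NIH Examiner, the protocol article classifies each participant as showing reliable change or not: "This will allow for a categorial YES/NO variable for the chi-square tests". It then plans two things. The first is "Chi-square tests will be used for week 3 and 6 reliable change indexes". The second is to follow the intervention effect over several time points, "namely at baseline, week 3 and 6 of the treatment", and for this it states: "This will be performed by means of chi-squares, with time as within subject factor and intervention as between subject factor".

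The Long-Term Effects paragraph opens with "Assessments at 3 and 6 months of follow-up will be critical for understanding the longterm effects of the intervention", applies the reliable change index "for the primary (i.e., UFOV) and secondary endpoints such as the NIH EXAMINER", and fixes the same method: "This will be performed by means of Chi-squares, with time as within subject factor and intervention as between subject factor". The long-term EEG analysis is different in kind: "participants will also perform the EEG, in order to allow for the correlation between changes in α- power" and other EEG measures with the reliable change indexes.

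No method for repeated binary outcomes (McNemar, Cochran's Q, GEE, mixed logistic regression) is named anywhere in the article.

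**The concern.** A Pearson chi-square treats every count as coming from a different participant. It has arms and categories but no within-subject factor. The plan attaches one to it, for YES/NO results that come from the same people at successive visits and are all measured against the same baseline. Such results are very likely to be positively correlated within a person.

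For the continuous UFOV score, the Primary Outcome paragraph uses the same factor structure with a mixed ANOVA, which can carry it. Chi-square cannot. The list of time points for the NIH EXAMINER also includes baseline, where a change from baseline has no YES/NO value.

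In the Long-Term Effects paragraph this is the only between-arm test named for UFOV and NIH EXAMINER. The Discussion relies on reliable change at those visits to separate lasting effects from placebo effects. If the analyst carries out the sentence in the most obvious way, the p-values behind those statements will be wrong.

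**Working it through.** **The plan's own figure.** The article states no error rate for the chi-square analyses. Its sample size is used here only to fix n. It can be reproduced with a difference of 56.2 − 31.5 = 24.7 and a pooled SD of √((74.8² + 43.7²)/2) = 61.26, so d = 0.403. A two-sample t-test with alpha 0.05 (two-sided assumed) and power 0.80 needs 97.5, rounded up to 98 per group. Then 98/0.90 = 108.9, so 109 per group, and 3 × 109 = 327. The pooled SD is inferred, because the article does not show this step.

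**Inputs.**
- From the article: three arms with equal allocation, 98 evaluable participants per arm, nominal alpha 0.05.
- Binary results per participant: two at weeks 3 and 6; two at 3 and 6 months, or three if the 1-month visit is included.
- Assumed, not in the article: within-person correlation ρ of the binary results from 0.3 to 0.7; a YES rate of 20% or 40%; visits entered as independent rows.

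**Pooled comparison of arms (2 df).** With k stacked visits, the variance of an arm total is inflated by D = 1 + (k − 1)ρ. For 2 df, P(χ² > x) = exp(−x/2), so the true error is exp(−5.991/(2D)).

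| ρ | k = 2: D | error | k = 3: D | error |
|---|---|---|---|---|
| 0.3 | 1.3 | 0.100 | 1.6 | 0.154 |
| 0.5 | 1.5 | 0.136 | 2.0 | 0.224 |
| 0.7 | 1.7 | 0.172 | 2.4 | 0.287 |

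**Time and arm-by-time.** These contrasts compare visits within the same people, so the variance is multiplied by 1 − ρ and the test errs the other way. For two visits the arm-by-time test has 2 df, and its error is exp(−5.991/(2(1 − ρ))). At ρ = 0.3 this is exp(−4.279) = 0.014, and at ρ = 0.5 it is exp(−5.991) = 0.0025.

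**Simulation under the null** (98 per arm, 10,000 trials per setting, ρ about 0.3 to 0.7):

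| Test | Type I error |
|---|---|
| Arms pooled over 2 stacked visits | 0.100–0.170 |
| Arms pooled over 3 stacked visits | 0.152–0.292 |
| Time, stacked | 0.000–0.019 |
| Arm-by-time, stacked | 0.000–0.014 |
| Global test over all arm-by-visit cells | 0.041–0.061 |
| Chi-square at a single visit | 0.046–0.054 |

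The simulation agrees with the formulas. The size and the direction of the error depend on which effect is tested.

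**The case against.** The strongest reply has four parts.

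- **The authors call time a within-subject factor, so they see the pairing.** That is fair, and it is why one cannot say that the plan counts each participant two or three times as independent. A reader might infer this, but the article never says that visits will be stacked. The wording could be shorthand for a paired test, yet McNemar's test and Cochran's Q have no between-subject factor, so neither fits the stated design.
- **The sentence is about change over time, where stacking is conservative.** This stands. A reader might infer that all the p-values would be too small. That holds only for a pooled comparison of arms over stacked visits, which the article does not describe. For time and arm-by-time the harm is lost power.
- **The week 3 and week 6 chi-squares come first and are sound.** This also stands. Run visit by visit, they use one result per participant, so the short-term transfer question does not rest on the faulty sentence. The Long-Term Effects paragraph has no such single-visit statement.
- **A journal article leaves detail to the analysis plan.** This would answer an omission. Here a method is named, twice, and it cannot do what is asked of it.

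It is also too wide to say that all long-term results are affected, since the EEG correlations do not use this test. Nor does the figure for three visits apply automatically: that paragraph opens with 3 and 6 months and names the 1-month visit only for EEG, although the trial design section schedules similar assessments at all study points.

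**Conclusion.** The point holds as an error in the stated method. Both paragraphs fix an analysis that an ordinary chi-square cannot perform, and nothing else in the article repairs it.

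The numerical consequence is conditional on three things: visits stacked as independent rows, a correlation of 0.3 to 0.7, and the particular effect tested. On those assumptions the pooled arm comparison runs at about two to six times the nominal 0.05, and the time and arm-by-time tests at well under half of it. None of these figures is a prediction of what the trial will report.

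The point covers the across-visit reliable-change tests for NIH EXAMINER during treatment, and for UFOV and NIH EXAMINER at follow-up. Severity is moderate, because these are secondary and long-term analyses in a trial described as exploratory.

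**What to change.** Restrict chi-square to one visit at a time, and say so in both paragraphs. For the analysis across visits, replace the chi-square sentence in both places with a GEE or mixed logistic model of the YES/NO reliable-change result, with arm, visit and arm-by-visit terms and the participant as the cluster. Only post-baseline visits enter the model. State whether the long-term model uses 3 and 6 months or also 1 month.

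The cost is two reworded sentences and slightly more analysis work, best settled before results are seen. These models are meant to hold the nominal 0.05, but that was not simulated here. The reliable-change endpoint can stay. Replacing it with a model of the continuous score would be a preference and is not needed to correct this error.
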